#### Implementation

After prescreening and eligibility for the trial confirmed, and baseline self-report questionnaires completed (to obtain Nijmegen score for stratification purposes), the physiotherapist will contact the participant and inform them of their group allocation (randomisation) according to the randomisation allocation provided by REDCap.

### Blinding

The physiotherapists will deliver the intervention to participants in an unblinded manner. The research assistant (RA), who will be administering the outcome measures, as well as the statisticians involved in data analysis, will be blinded to treatment allocation while the trial is active. After randomisation, participants will be asked not to reveal their group allocation to the RA. Given many of the outcome measures will be administered electronically (via REDCap), this will also assist RA blinding.

### Participant safety and withdrawal

Participants will be withdrawn from the trial in any of the following circumstances:

At their own volition/withdrawal of consent.Emergence of epileptic seizures.Emergence of significant AEs, at request of the participant, or discretion of their clinician

If the participant wishes to withdraw, they will be asked to attend a brief telephone/in-person interview (the latter if convenient) to review their reason for withdrawal, the occurrence of AEs, as well as frequency of their FS (to gauge if the treatment has caused any worsening in clinical features). We will also ask them to sign the withdrawal of consent form to formally document their discontinuation and indicate if they wish for their data to be excluded from the analysis. We will, however, respect their wishes if they decline to partake in this exit interview.

If a participant self-reports to the study team (eg, during a routine study visit), or if a member of the study team identifies in the patient medical records a new diagnosis of epilepsy or the emergence of epileptic seizures, the participant will be withdrawn from the study. The diagnosis must be confirmed by an epileptologist. The participant will then be notified of their withdrawal from the trial and the reason for it. The standard withdrawal of consent procedure described above will be followed.

No withdrawn participants will be replaced.

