## Methods and analysis

### Trial design

A 24-week, multicentre, individually-randomised, assessor-blinded, two-arm, parallel-group efficacy and acceptability trial of BCT versus control (Befriending) in 220 participants ≥16 years of age with FS. Eligible participants will be randomly allocated (1:1) to receive two sessions of either BCT or Befriending with a respiratory physiotherapist over a 4-week period. They will complete assessments at baseline (prior to commencing treatment) and 4 weeks, 12 weeks and 24 weeks post their initial session of BCT/Befriending. The trial will be conducted alongside their standard care (treatment as usual). Optional, longitudinal observational follow-up will be conducted 52 weeks, 78 weeks and 104 weeks after their initial treatment session.

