### Statistical analysis

A formal detailed statistical analysis plan for the study will be written prior to unblinding of the database. All analyses will follow the intention-to-treat principle.

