#### Secondary outcomes

Binary outcomes will be analysed similarly to the primary outcome; continuous outcomes will be analysed using a Longitudinal Data Analysis model.^37^ Any markedly skewed continuous outcomes will be transformed before analysis. The acceptability of BCT captured by a tailored self-report questionnaire provided after attending the Week 4 ‘booster’ session and adverse events will be reported by study group and visit.

The statistical models for the primary and secondary outcomes will provide valid inference in the presence of missing data if the missing data mechanism is missing at random.

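### Significant AEs or new epilepsy can end a participant's place in the trial, not only the intervention, so Week 12 outcomes and later safety data can be lost for post-randomisation reasons

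*Protocol article*

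**What the plan says.** The section Participant safety and withdrawal opens with "Participants will be withdrawn from the trial in any of the following circumstances". Three circumstances follow: the participant's own wish, epileptic seizures, and "Emergence of significant AEs, at request of the participant, or discretion of their clinician".

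A participant who wishes to leave is asked to an exit interview, which may be declined. It covers the reason, AEs and current seizure frequency. The participant is also asked to sign a withdrawal-of-consent form, which lets them ask for their data to be left out of the analysis. Nobody is replaced.

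For a new epilepsy diagnosis the rule is firmer: "the participant will be withdrawn from the study. The diagnosis must be confirmed by an epileptologist". The participant is then notified, and "The standard withdrawal of consent procedure described above will be followed".

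Under Trial design, participants "receive two sessions of either BCT or Befriending with a respiratory physiotherapist over a 4-week period". BCT home exercises continue to Week 12 (Table 2; Adherence). The primary outcome is zero seizures in the four weeks before Week 12, from the participant's diary (Box 1). Safety is a secondary outcome, reviewed at Weeks 4, 12 and 24.

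Under Statistical analysis: "All analyses will follow the intention-to-treat principle". Under Secondary outcomes, the models for primary and secondary outcomes are said to give "valid inference in the presence of missing data if the missing data mechanism is missing at random".

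**The concern.** Three matters are run together: stopping the intervention, stopping follow-up and withdrawing consent. The text moves from the occurrence of an event straight to leaving the trial. Someone who did not ask to leave can therefore lose their Week 12 outcome, and in the epilepsy case is also invited to remove the data already given.

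At stake are the primary comparison and the safety record. Under Risk management and safety, AEs include worsening of a pre-existing condition and new symptoms. The reason for withdrawal can therefore overlap with the outcome being measured, and that is the setting in which missing at random is hardest to defend. The same people also drop out of AE enquiry at later visits, although their safety follow-up is of most interest. No analysis plan can recover outcomes that the protocol stops collecting.

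**Working it through.** **1. The provisions side by side**

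| Provision | Section | Effect |
|---|---|---|
| Leaves the trial for significant AEs or epileptic seizures | Participant safety and withdrawal | No later diary, questionnaire or AE enquiry is described |
| Exit interview records seizure frequency | Same | Taken at withdrawal, not at Week 12, and may be declined |
| Consent-withdrawal procedure used for epilepsy | Same | Data exclusion offered to people who did not ask to leave |
| Intention to treat | Statistical analysis | Needs outcomes on everyone randomised, as far as possible |
| Missing at random | Secondary outcomes | Needs the loss to be explained by data already observed |

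**2. The plan's own sample size**

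Inputs (Sample size calculation): 40% v 20%, 80% power, two-sided 5%, 25% drop-out.

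n per arm = [1.96 × √(2 × 0.30 × 0.70) + 0.8416 × √(0.40 × 0.60 + 0.20 × 0.80)]² / 0.20² = (1.270 + 0.532)² / 0.04 ≈ 81.2, so 82.

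82 / (1 − 0.25) = 109.3, so 110 per arm and 220 in total. This agrees with the plan.

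**3. How large the bias could be**

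The documents give no rate of withdrawal for AEs or epilepsy, so w and r below are assumptions. Let p be the true remission rate in an arm, w the share of the arm withdrawn before Week 12, and r the remission rate those people would have had. On a complete-case approximation:

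observed rate = (p − w × r) / (1 − w), so bias = w × (p − r) / (1 − w).

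Worst case with no true effect: p = 20% in both arms, withdrawals in BCT only, r = 0.

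| w in BCT | Observed BCT rate | Spurious difference | Type I error (nominal 5%) |
|---|---|---|---|
| 2% | 0.20 / 0.98 = 20.4% | +0.4 points | 5.1% |
| 5% | 0.20 / 0.95 = 21.1% | +1.1 points | 5.4% |
| 10% | 0.20 / 0.90 = 22.2% | +2.2 points | 6.8% |

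Type I error uses the normal approximation with 110 × (1 − w) in BCT and 110 in Befriending, ignoring other drop-out.

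**4. How far the result depends on the assumptions**

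- w = 10% in BCT, r = 20% (the arm's own rate): 0.10 × (0.20 − 0.20) / 0.90 = 0.
- w = 10% in BCT, r = 40%: 0.10 × (0.20 − 0.40) / 0.90 = −2.2 points, against BCT.
- w = 10% in BCT and 5% in Befriending, r = 0 in both: 22.2% − 21.1% ≈ +1.2 points (0.2222 − 0.2105 = 0.0117).
- w = 10% in both arms, r = 0, no true effect: difference 0.
- w = 10% in both arms, r = 0, true rates 40% v 20%: 44.4% − 22.2% = 22.2 points instead of 20.

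**The case against.** Much can be said on the other side.

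- **Direction of bias.** A reader might infer that BCT will look better than it is. The documents do not support that. They give no withdrawal rates by arm, and the pilot reported no AEs. The expected BCT side effects are described as transient and manageable in the session, and nothing says they are the significant AEs that lead to withdrawal. Nothing links new epilepsy to either arm. With comorbid epilepsy excluded and the diagnosis confirmed on video EEG, such cases may be few.
- **Treatment left to stop.** A reader might also infer that, with sessions over at Week 4, withdrawal does nothing except end data collection. That is wrong: BCT home exercises run to Week 12.
- **Automatic withdrawal.** For AEs it is not automatic. It rests on the participant's request or the clinician's discretion, and someone who wants to leave altogether may decline follow-up whatever the wording.
- **The planned model.** It is longitudinal and adjusts for baseline seizure frequency. Data from before withdrawal stay in unless exclusion is requested, so the complete-case figures are only an approximation. Withdrawal after Week 12 leaves the primary outcome untouched.
- **Intention to treat.** Analysing people as randomised with a likelihood model is not in itself contrary to it, and missing at random is stated openly as a condition.
- **A condensed article.** The full protocol may provide for follow-up after withdrawal.

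These points limit the size and certainty of any bias. They do not remove the rule as published. It withdraws people from the trial, and it expressly applies the consent-withdrawal procedure, with its data-exclusion offer, to people who have not withdrawn consent.

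**Conclusion.** The point holds as a design weakness that can be corrected cheaply, not as a demonstrated bias. Followed as written, the rule loses the primary outcome for anyone withdrawn before Week 12 for an AE or epilepsy, and loses their later safety data. It weakens the intention-to-treat analysis, most plainly through the data-exclusion offer, and it leaves missing at random doubtful for these losses.

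The bias could favour BCT if withdrawals are more frequent there or fall mostly on non-remitters. The worst-case range of +0.4 to +2.2 points rests on assumed BCT-only withdrawal of 2% to 10%, every case a non-remitter, no true effect, and a complete-case approximation to the planned model. Other assumptions give zero or a bias against BCT. The planned sample size is unaffected.

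**What to change.** - Define two separate statuses: stopping the intervention and stopping follow-up. Leave the decision to stop the intervention where it now lies.
- Keep the withdrawal-of-consent procedure, and the option to exclude data, for participants who themselves withdraw consent.
- For AE and epilepsy cases who still agree, continue the scheduled diary, questionnaires and AE enquiry to Week 24, and analyse them in the arm to which they were randomised.
- Add a sensitivity analysis in which those withdrawn for AEs or epilepsy whose Week 12 outcome is still missing count as non-remitters, by the same rule in both arms.

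The cost is an amendment to the protocol and consent wording, and modest extra follow-up using contacts already in the schedule. Recruitment opened in February 2024 and is expected to run for four years, so an amendment can still protect outcomes. One limit remains: once epilepsy emerges, a self-kept diary may not reliably separate functional from epileptic events, so those Week 12 records should be flagged and interpreted with care.

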### Concomitant care

The BCT/Befriending will be used in addition to the participants’ standard care, that is, they will continue their ‘treatment as usual’ (TAU) while they are enrolled in the trial. Standard care can vary widely in this patient group, particularly when newly diagnosed with FS. For example, some patients may be taking (or withdrawing from) antiseizure medications and/or other pharmacotherapies; see a neuropsychiatrist, psychologist or other allied health professionals; whereas others may not be receiving treatment. There are no restrictions on what standard care can/cannot entail while they participate in the trial; however, if they are engaging in therapies which focus on specific breathing techniques (eg, box breathing, Buteyko method), they will be excluded from the trial.

Study staff will record all concomitant therapies at baseline and follow-up appointments, assisted by a tailored, self-reported Resource Use Questionnaire (RUQ), and for consenting Australian participants, accessing Medicare Benefits Schedule (MBS) and Pharmaceutical Benefits Scheme (PBS) data from Services Australia. For consenting Australian participants living in Victoria, health service use data (hospital admissions, emergency department presentations and community healthcare services) will also be retrieved from The Centre for Victorian Data Linkage (CVDL). Collectively, these data will capture what each participant’s TAU entails, as well as changes to TAU throughout the trial.

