Box 1OutcomesPrimarySeizure remission, defined as seizure frequency of zero in the preceding 4 weeks (recorded by the participant in a seizure frequency diary), measured at Week 12 (12 weeks post the initial treatment session).SecondaryChanges in hyperventilation from baseline, measured by the Nijmegen scale of hyperventilation provided at baseline, Week 4, Week 12 and Week 24.Changes in healthcare utilisation from baseline, measured via a tailored resource use questionnaire provided at baseline, Week 12 and Week 24, as well as changes in health service use ascertained from Services Australia and CVDL data (Services Australia and CVDL data for consenting participants only).Changes in quality of life from baseline, measured by the Assessment of Quality of Life Eight Dimension provided at baseline, Week 4, Week 12 and Week 24.Changes in depression and anxiety symptoms from baseline, measured by the 9-item Patient Health Questionnaire and Generalised Anxiety Disorder Assessment respectively, provided at baseline, Week 4, Week 12 and Week 24.Changes in occupational and social functioning from baseline, measured by the Work and Social Adjustment Scale provided at baseline, Week 4, Week 12 and Week 24.Acceptability of BCT captured by a tailored self-report questionnaire provided after attending the Week 4 ‘booster’ session.Safety of BCT assessed by the occurrence of adverse events reviewed at Week 4, Week 12 and Week 24.tcCO_2_ levels (mm Hg; a marker of hyperventilation) preceding or during seizures, BPAT score (at baseline) and/or Nijmegen score (at baseline), to predict response to treatment.ExploratoryThe presence of significant life events in childhood and adolescence (≤16 years of age), and 12 months preceding the onset of their FS, assessed via the Childhood Experience of Care and Abuse Questionnaire and the LEDS*, respectively, to gauge moderators of treatment response.The MDI and Toronto Alexithymia Scale provided at baseline will be assessed if predictors of treatment response. MDI scores at Week 4, Week 12 and Week 24 will be assessed if they correlate with treatment response.*Note, the LEDS is optional, and only relevant to participants whose FS have started within the last 2 years.BCT, breathing control training; BPAT, Brompton Breathing Pattern Assessment Tool; CVDL, Centre for Victorian Data Linkage; FS, functional seizures; LEDS, Life Events and Difficulties Schedule; MDI, Multiscale Dissociation Inventory; tcCO_2_, transcutaneous carbon dioxide.

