Box 2Trial schematicClinical assessment (neurologist)Functional seizures diagnosis confirmed by epileptologist.Participant informed of trial.Informed consent obtained OR obtain consent for study staff to follow-up and discuss.PrescreeningEligibility confirmed using prescreening questionnaire.Informed consent (if not completed by referring clinician).Baseline study questionnaires completed: Demographics, The Assessment of Quality of Life Eight Dimension (AQoL-8D), Generalised Anxiety Disorder Assessment (GAD-7), Patient Health Questionnaire, 9-item (PHQ-9), Multiscale Dissociation Inventory (MDI), Nijmegen, Toronto Alexithymia Scale, Resource Use Questionnaire (RUQ), Seizure triggers and control, Seizure quality, Work and Social Adjustment Scale (WSAS).Medical record data extracted.RandomisationPhysiotherapist contacts participant to inform them of their group allocation and schedule first session.Initial treatment session (Breathing Control Training/Befriending): baseline60 min, one-on-one session with physiotherapist, conducted at clinical care site (or Telehealth if required).Seizure frequency and adherence diary provided.Booster treatment session (Breathing Control Training/Befriending): week 430 min, one-on-one session with physiotherapist, conducted at clinical care site (or Telehealth if required).Adverse events, seizure frequency and adherence diary reviewed by physiotherapist.Research assistant (blinded) sends self-report questionnaires to participant via Research Electronic Data Capture (REDCap): *AQoL-8D, Acceptability, GAD-7, PHQ-9, MDI, Nijmegen, Seizure quality, WSAS.*Primary endpoint: week 12Research assistant (blinded) sends participant self-report questionnaires via REDCap: *AQoL-8D, Childhood Experience of Care and Abuse Questionnaire, GAD-7, PHQ-9, MDI, Nijmegen, RUQ, Seizure triggers and control, Seizure quality, WSAS.*Adverse events and medication status reviewed by research assistant.For eligible and willing participants, invited to complete Life Events and Difficulties Schedule.Follow-up: week 24Research assistant (blinded) sends participant self-report questionnaires via REDCap: *AQoL-8D, GAD-7, PHQ-9, MDI, Nijmegen, RUQ, Seizure quality, WSAS.*Participants randomised into the Befriending (control group) offered access to the BCT intervention.Observational follow-up: week 52, week 78 and week 104 (optional)Participants sent self-report questionnaires via REDCap: *AQoL-8D, GAD-7, PHQ-9, MDI, Nijmegen, RUQ, WSAS, seizure frequency (for previous 4*

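### Intention-to-treat is promised, but the stated rules let randomised participants leave the analysis or have no Week 12 outcome, possibly in relation to arm and outcome

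*Protocol article*

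**What the plan says.** The analysis principle is unqualified: "All analyses will follow the intention-to-treat principle" (Statistical analysis).

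Four other rules bear on it.

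- **Withdrawal form.** Participants who wish to leave are asked to sign a form on which they "indicate if they wish for their data to be excluded from the analysis" (Participant safety and withdrawal).
- **Withdrawal by the team.** The listed grounds include "Emergence of significant AEs, at request of the participant, or discretion of their clinician". For "a new diagnosis of epilepsy or the emergence of epileptic seizures, the participant will be withdrawn from the study", the article adds: "The standard withdrawal of consent procedure described above will be followed". Withdrawal is from the trial. An exit interview asks about seizure frequency at that moment, and no later outcome collection is described.
- **Time origin.** Remission is "measured at Week 12 (12 weeks post the initial treatment session", as Box 1 puts it. Before that session the physiotherapist "contacts participant to inform them of their group allocation and schedule first session" (Box 2; Allocation, Implementation, says the same). Box 2 has the seizure diary handed over at the session. The only earlier seizure record in Table 3 is the prescreening count.
- **Breathing therapies.** Concomitant care, in a sentence about what usual care may include during participation, says: "if they are engaging in therapies which focus on specific breathing techniques (eg, box breathing, Buteyko method), they will be excluded from the trial". Table 1 lists this as an eligibility exclusion, and the withdrawal list does not contain it.

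**The concern.** Intention-to-treat means that everyone randomised is analysed in the allocated arm, whatever happened afterwards. A form that offers to take already collected data out of the analysis works against that, because the choice is made after the participant knows the arm and how the seizures have gone. Withdrawing someone from the trial before Week 12, when stopping the sessions might have been enough, loses the primary outcome. Starting the clock and the diary at a session held after disclosure leaves non-attenders with nothing to measure.

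Participants are unblinded and the primary outcome is a self-kept diary. If people who are doing badly in one arm leave more often than in the other, the remission comparison is biased. Recruiting more people does not remove that bias, and outcomes never collected cannot be recovered by a later analysis plan.

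**Working it through.** **1. The plan's own figure.** Inputs from Sample size calculation: 40% v 20%, two-sided 5%, 80% power, 25% dropout, 1:1.

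Pooled-variance formula, no continuity correction: n = [1.96·√(2·0.30·0.70) + 0.842·√(0.40·0.60 + 0.20·0.80)]² / 0.20² = 81.2, so 82 per arm. Then 82/0.75 = 109.3, so 110 per arm and 220 in total. The stated figure reproduces.

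Power with 110·0.75 = 82.5 per arm is 80.6%. It would be 77.8% at 30% loss and 74.7% at 35%. Losses inside the 25% allowance therefore do not take power below target. The issue is bias, not size.

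**2. The rules followed for three randomised participants.**

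| Participant | Rule applied | Result |
|---|---|---|
| Withdraws and ticks the exclusion option | Withdrawal form | Collected diary data leave the analysis |
| Withdrawn by the team at, say, Week 6 | Withdrawal from the trial | Data to Week 6 stay unless exclusion is requested; no Week 12 outcome |
| Learns allocation, never attends session 1 | Clock and diary start at session 1 | No Week 12 date, no prospective diary |

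The first breaches intention-to-treat directly. The second and third produce a missing primary outcome through the design of the procedures.

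**3. Possible size.** The documents give no frequencies, so the fractions here are assumptions. Let true remission be 20% in both arms, and let a fraction x of non-remitters leave one arm, with no remitters lost and nobody lost from the other arm.

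Observed rate = 0.20 / [0.20 + 0.80·(1 − x)].

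- x = 0.10: 0.20/0.92 = 21.7%, a spurious 1.7 points.
- x = 0.25: 0.20/0.80 = 25.0%, a spurious 5.0 points.

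False-positive probability for a pooled two-sided z-test is Φ[(d − 1.96·s₀)/s₁] + Φ[(−d − 1.96·s₀)/s₁]. Here d is the difference, s₀ the pooled and s₁ the unpooled standard error. For x = 0.25 and 82.5 per arm, s₀ = √(0.225·0.775·2/82.5) = 0.0650 and s₁ = √((0.1875 + 0.16)/82.5) = 0.0649. This gives Φ(−1.19) + Φ(−2.73) ≈ 0.12.

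| x | Non-remitters lost of 88 in an arm of 110 | Exact, 82 per arm | Exact, 110 per arm less those lost |
|---|---|---|---|
| 0.10 | about 9 | 5.9% | 6.3% |
| 0.25 | 22 | 12.0% | 13.5% |

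If the other arm also loses non-remitters, the bias shrinks: 25% in one arm and 10% in the other leaves 25.0 − 21.7 = 3.3 points, and equal fractions leave none.

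**4. Whether the planned model covers this.** Secondary outcomes says the models are valid if data are missing at random. That holds if loss depends only on what the model retains: arm, site, Nijmegen stratum, baseline seizure frequency and observed earlier visits. It does not hold if loss depends on the unseen Week 12 outcome given those. Data excluded on request also take away the earlier visits that would help the assumption. A never-attender has no post-baseline outcome for the model to use.

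**The case against.** A right to withdraw is ordinary, the form has ethics approval, and a participant's wish about their data may have to be honoured. That stands, and it is why the remedy is framed as a default within what consent allows. It does not reconcile the option with an unqualified intention-to-treat statement.

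A second objection is that stopping follow-up only creates missing data, and that the handling of never-treated participants belongs in the analysis plan. This is right for the analysis. It is not right for collection: whether a diary exists at Week 12 is settled by trial procedures.

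Several stronger readings are tempting but unsupported.

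- A reader might infer that data are deleted. The text speaks only of exclusion from the analysis.
- A reader might infer that everyone withdrawn by the team gets the exclusion option. The article extends the procedure explicitly to epilepsy cases and is silent on adverse-event withdrawals at a clinician's discretion. Nor does it say that team-withdrawn participants' earlier data leave the analysis unless they ask.
- A reader might infer that controls who take up breathing therapy are removed. The sentence is ambiguous, and both Table 1 and the withdrawal list fit a screening criterion.
- A reader might infer that every route depends on arm. No link between emergent epilepsy and arm is stated. The expected effects of breathing training are described as transient and manageable in the session, and the pilot reported no adverse events. Arm-dependence is possible, not shown.
- A reader might take 12% as the expected error rate. It is a one-sided worst case; the 10% case gives about 6%.

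**Conclusion.** The point stands as something that should be fixed. The withdrawal form conflicts with the intention-to-treat statement. Trial-level withdrawal and a time origin after disclosure leave some randomised participants without the primary outcome. With assumed one-sided exclusion of 10% to 25% of non-remitters, the spurious difference is 1.7 to 5.0 points against a target of 20, and the false-positive rate is about 6% to 13.5%. These figures rest on no remitters being lost and no loss in the other arm; real losses may be smaller or may offset. The sample size of 220 is correctly derived and needs no change.

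**What to change.** Leave the clinical withdrawal criteria unchanged and alter the data rules.

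1. By default, keep data collected up to withdrawal in the analysis. Let the form offer to stop further collection, as far as ethics approval and consent allow. Report any exclusions by arm.
2. Separate stopping sessions from stopping follow-up. Ask those who stop sessions, or whom the team withdraws, to continue the diary and the Week 4, 12 and 24 questionnaires unless they decline. Analyse them as randomised.
3. Issue the seizure diary at randomisation, and define a Week 12 date for those who never attend session 1, for example from the booked session date or the randomisation date.
4. Reconcile Concomitant care, Table 1 and the withdrawal list on whether breathing therapy is a screening exclusion only.

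The cost is an ethics amendment to the form, a few sentences in the protocol and some extra follow-up. Recruitment opened in February 2024 and is planned to run for four years, so an early change protects more of the sample.

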**Ethics and dissemination:**

The study has been approved by The Austin Health Human Research Ethics Committee (HREC/84335/Austin-2022) and the New Zealand Central Health and Disability Ethics Committee (2022 FULL 12324). Findings will be reported to trial participants and consumers; presented at local, national and international conferences; and disseminated by a peer-reviewed scientific journal.

STRENGTHS AND LIMITATIONS OF THIS STUDYThe study has a large sample, and an international, multicentre design.The study uses a control arm matching the intervention for therapist time, and delivered by the same therapist.The study is only blinded to assessor; participant and therapist blinding is not possible.

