### Outcomes

Primary, secondary and exploratory outcomes are outlined in table 2, box 1.

**Table 2 T2:** Procedures in the trial that are in addition to standard care (alongside ‘treatment as usual’)

Procedure	Time/visit	Dosage/volume
BCT/Befriending sessions	Baseline and 4 weeks later	60 min initial session; 30 min second session
Seizure frequency diary	Completed by the participant as seizures occur throughout the 24-week study period	~1 min per week
Breathing exercises (BCT participants only) and adherence diary	Following the baseline session, through to Week 12	5–10 mins, two times a day
Self-report questionnaires	Baseline, Week 4, Week 12 and Week 24	30–45 mins
LEDS (optional)	Week 12	LEDS (optional) Week 12 ~2 hours

BCT, breathing control training; LEDS, Life Events and Difficulties Schedule.

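### Withdrawing participants may have their data left out of the analysis, which conflicts with an intention-to-treat statement that allows no exception

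*Protocol article*

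**What the plan says.** The section Participant safety and withdrawal lists three routes out of the trial: the participant's own decision, emergence of epileptic seizures, and significant adverse events. A participant who wishes to leave is invited to an exit interview and asked to sign a withdrawal form, on which they "indicate if they wish for their data to be excluded from the analysis". The text does not restrict the request to particular data, reasons or times. For participants the team withdraws because of epilepsy, it adds: "The standard withdrawal of consent procedure described above will be followed". It also says "No withdrawn participants will be replaced".

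The Statistical analysis section says "All analyses will follow the intention-to-treat principle" and names no exception. Under Secondary outcomes, the validity of the models is made to rest on data being missing at random.

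Three further statements bear on who would make such a request:
- The strengths and limitations list says "The study is only blinded to assessor; participant and therapist blinding is not possible". The Implementation section has the physiotherapist tell each participant their allocation.
- The primary outcome, remission at Week 12, is "recorded by the participant in a seizure frequency diary".
- Table 2 describes that diary as "Completed by the participant as seizures occur throughout the 24-week study period", so participation continues for 12 weeks after the primary endpoint.

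**The concern.** A randomised person whose data are left out on request is not analysed as randomised, so the two statements cannot both hold for that person. The request comes from someone who knows their arm and how they have fared, and it can come after their own Week 12 result is known. Exclusion can therefore depend on arm and outcome.

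What is lost depends on timing. For someone leaving before Week 12, exclusion also takes away the baseline and early follow-up data that make missing at random more plausible in a repeated-measures model. For someone leaving after Week 12, it takes away a primary outcome that was observed.

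Safety is exposed as well. Significant adverse events are a listed reason for withdrawal and safety is a secondary outcome, yet the exclusion option has no carve-out for safety data.

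**Working it through.** **1. The plan's own figure.** Inputs from the sample size section: remission 40% v 20%, 80% power, 5% two-sided, 25% drop-out.

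n per arm = [1.96·√(2·0.3·0.7) + 0.8416·√(0.4·0.6 + 0.2·0.8)]² / 0.20² = (1.2702 + 0.5323)² / 0.04 = 81.2, rounded up to 82.

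82 / (1 − 0.25) = 109.3, rounded up to 110 per arm, 220 in total. The stated figure is reproduced, so sample size is not at issue.

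**2. The statements side by side.** The withdrawal section permits exclusion for any leaver, for any data and at any time. The Statistical analysis section covers all analyses without exception. Nothing in the document says which prevails.

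**3. Size, as a labelled hypothetical.** The documents give no request rate, so every count k below is an assumption. I take 110 per arm, remission of 44/110 in BCT and 22/110 in control, no other missing data, and k non-remitters in one arm only who exclude themselves after their Week 12 outcome is recorded. The reported proportion in that arm becomes remitters / (110 − k).

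| k | BCT non-remitters exclude | Difference from 20% | Control non-remitters exclude | Difference from 40% |
|---|---|---|---|---|
| 3 | 44/107 = 41.1% | 21.1 points | 22/107 = 20.6% | 19.4 points |
| 5 | 44/105 = 41.9% | 21.9 points | 22/105 = 21.0% | 19.0 points |
| 8 | 44/102 = 43.1% | 23.1 points | 22/102 = 21.6% | 18.4 points |
| 11 | 44/99 = 44.4% | 24.4 points | 22/99 = 22.2% | 17.8 points |

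The true difference is 20 points throughout. The direction of the error depends on which arm asks.

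**4. Type I error under the same one-sided pattern.** This comes from a simulation of 400,000 trials with true remission 20% in both arms, a pooled two-proportion z-test, and a share q of BCT non-remitters excluded.

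| q | Mean exclusions | Two-sided type I error |
|---|---|---|
| 0 | 0 | 4.9% |
| 5% | 4.4 | 5.3% |
| 10% | 8.8 | 6.1% |
| 20% | 17.6 | 10.2% |

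A handful of requests matters little. The rate becomes clearly inflated only with many one-sided requests.

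**5. Exclusions unrelated to outcome, equal in both arms.** Power = Φ[(0.20·√n − 1.2702) / 0.6325], which gives 90.5% at n = 110 per arm, 87.3% at 99 and 80.9% at 83. Only power is lost.

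**6. Leavers before Week 12.** Someone who leaves early and is not followed further has no Week 12 diary outcome whether or not they ask for exclusion, so the table in step 3 does not measure the effect of the option for them. What the option adds is the loss of their earlier data from the mixed model.

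**The case against.** The strongest case against is that this is a small matter of clarification. The full analysis plan, the consent form and the withdrawal form are not shown. The option may be a consent or ethics requirement, and handling of revoked consent often sits in the analysis plan. This stands in part: an analysis plan can define the exception and add sensitivity analyses. It cannot, however, fully undo a promise of exclusion already given to participants.

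Three stronger readings are tempting, and the documents do not support them.

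- A reader might infer that the records are destroyed and that no analysis could repair the bias. The text says excluded from the analysis, not deleted, and Record retention and storage keeps data for at least 15 years. If requests depended only on arm and the covariates in the model, the adjusted estimate need not be biased.
- A reader might take the 1 to 3 point shift for 3 to 8 exclusions as the expected bias. It applies in full only to exclusions after a recorded Week 12 outcome, rests on assumed one-sided counts, and could run the other way.
- A reader might infer that 25% of 220, or 55 people, will be offered the choice. That figure is planned drop-out of every kind, and people who simply stop responding need not sign any form. The protocol also calls 25% conservative and cites BCT attrition below 10%, which is under 11 of 110. So 55 is an upper bound on drop-out, not a count of likely requests.

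**Conclusion.** The concern holds as a conflict between two explicit statements: an open-ended exclusion option at withdrawal, and intention-to-treat for all analyses. The option permits exclusion that depends on arm and outcome. It does not show that this will happen. Size and direction are unknown because no request rate is given. With a few requests the effect on the estimate and on type I error is small; with many one-sided requests it is not. The point warrants reconciling the text while recruitment, which opened in February 2024 and is expected to run for 4 years, still has participants to come. It does not call the sample size or the choice of model into question.

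**What to change.** **For new participants.** State in the protocol, the consent form and the withdrawal form that withdrawal stops new data collection, and that data collected up to that point, including safety data, are kept and analysed as randomised.

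**Where existing consent, ethics or law requires a request to be honoured.** Declare it as an exception to intention-to-treat. Keep the randomised arm and date where permitted. Report the number and timing of exclusions by arm. Run sensitivity analyses for these participants, counting them as non-remission and as best and worst case by arm. In the hypothetical above, counting them as non-remission returns 44/110 = 40.0%.

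**Cost.** An amendment to the protocol, consent and withdrawal forms, reviewed by both ethics committees; two consent wordings within one trial; and a little more analysis. If the change were judged a significant design change, the Consent section would also require current participants to be contacted with an amended form. The sample size does not change.
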